**Fig. 2 Fig2:**
[figure not shown]
SPIRIT plan

### Sample size {14}

The study's sample size is based on the expected difference in outcome measure of the MMSE score between the two intervention groups. We determined this effect by reviewing the literature on repetitive transcranial magnetic stimulation's impact on stroke patients [28]. We used a 1:1:1 ratio between groups and calculated the power using G*Power free software (Version 15.0.5). In addition, considering the insufficient sample size caused by patient detachment during the research process, it is necessary to expand the sample size by 20%, resulting in a total sample size of 57 patients.

### Recruitment {15}

This study aims to enroll 57 individuals undergoing rehabilitation at Shanghai Herson Rehabilitation Hospital who have been recommended for rTMS treatment by their doctors or therapists. These individuals must also be willing to participate in the study. Once verbal consent is given to participate in the study, written and oral information regarding the research objectives and procedures will be provided to all participants. All personal information and other data regarding potential or registered patients can be tracked in medical records and obtained from the corresponding authors upon request to protect confidentiality. After receiving written informed consent from qualified screening participants, the study will begin with baseline evaluation and be randomly assigned.

## Assignment of interventions: allocation

### Sequence generation {16a}

To ensure fairness, an independent statistician uses SPSS.25 software to generate randomized allocations for eligible patients. The patients are then evenly distributed into three groups based on their rTMS parameters. The statistician has no involvement in evaluating or executing the experiment.

### Concealment mechanism {16b}

The results of random allocation and detailed rTMS plan are communicated by statisticians by phone to rTMS physical therapists and doctors.

### Implementation {16c}

A statistician uses SPSS.25 software to generate random numbers sorted by size. Numbers 1–19 are for the control group, 20–38 are for the single-target stimulation group, and 39–57 are for the double-target stimulation group. Patients are recommended by rehabilitation doctors, therapists, or any other doctor and voluntarily receive rTMS treatment. The doctor randomly assigns 57 patients to any of the three groups according to the results of the random sequence.

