### Who will take informed consent? {26a}

To determine eligibility for the study, neurologists will evaluate patients who meet the criteria mentioned above. Patients who meet the eligibility criteria will receive initial research details from their doctor and researchers. If they agree to participate, they will be given written information outlining the study's objectives and procedures, and they will sign an informed consent form.

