## Assignment of interventions: blinding

### Who will be blinded {17a}

The exact allocation and treatment plan are not disclosed to patients, as well as other researchers such as evaluators and analysts. And rTMS physical therapists are not involved in other research work, such as patient recruitment, randomization, allocation, outcome evaluation, and data analysis.

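### Allocation concealment is not secured as written: doctors are told the allocation and one of them makes the assignment, while doctors also recruit, and physician blinding is stated inconsistently

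*Protocol article*

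**What the plan says.** All references are to the protocol article.

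- **Generation.** Under Sequence generation {16a}, "an independent statistician uses SPSS.25 software to generate randomized allocations for eligible patients". That statistician takes no part in evaluating or running the trial.
- **Concealment.** Concealment mechanism {16b} is a single sentence: "The results of random allocation and detailed rTMS plan are communicated by statisticians by phone to rTMS physical therapists and doctors".
- **Implementation {16c}.** Random numbers are ranked and cut into three fixed sets: "Numbers 1–19 are for the control group, 20–38 are for the single-target stimulation group, and 39–57 are for the double-target stimulation group". On referral: "Patients are recommended by rehabilitation doctors, therapists, or any other doctor and voluntarily receive rTMS treatment". On assignment: "The doctor randomly assigns 57 patients to any of the three groups according to the results of the random sequence".
- **Recruitment {15}.** Participants are people "who have been recommended for rTMS treatment by their doctors or therapists". Written consent and baseline evaluation come before assignment.
- **Consent {26a}.** Neurologists assess eligibility, and "Patients who meet the eligibility criteria will receive initial research details from their doctor and researchers".
- **Blinding {17a}.** "The exact allocation and treatment plan are not disclosed to patients, as well as other researchers such as evaluators and analysts". The rTMS therapists are kept out of recruitment, randomisation, allocation, evaluation and analysis. No similar limit is set for doctors.
- **Unblinding {17b}.** None is foreseen.
- **Data monitoring committee {21a}.** One reason given for the committee is to keep researchers and physicians blinded.
- **Trial design {8}.** The trial is declared single-blind.

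**The concern.** Concealment means that whoever decides on a patient's entry cannot know the next arm. Here doctors as a group refer patients, inform them, receive the allocation and, in one sentence, make the assignment. The section that should describe the safeguard describes disclosure instead. The protocol recognises the principle, since it bars rTMS therapists from recruitment and allocation, but it does not extend that bar to doctors.

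Two things are at stake:

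- **Selection by arm.** If a recruiting doctor knew the next allocation, the choice or timing of referrals could follow it. With 19 patients per arm, a few such choices could shift baseline prognosis. The tests described in {20a} (one-way ANOVA with LSD-t, Kruskal–Wallis, paired t) do not adjust for baseline.
- **Care by arm.** Doctors who know the arm could vary the individualised medical care that {11d} permits. The scope is limited, because {6b} fixes the rehabilitation schedule and {11d} prohibits cognition-improving drugs.

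**Working it through.** **1. The plan's own figure.** Three sets of 19 give 3 × 19 = 57, which matches the stated total. The lists are internally consistent, and the concern is about who has access to them.

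**2. The sections side by side.**

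| Question | What the text gives | Where |
|---|---|---|
| Who generates the list? | Independent statistician | {16a} |
| Who recommends patients? | Their doctors or therapists, or any other doctor | {15}, {16c} |
| Who first informs patients? | Their doctor and researchers | {26a} |
| Who is told the allocation? | rTMS therapists and doctors | {16b} |
| Who assigns? | The doctor | {16c} |
| When is assignment? | After consent and baseline | {15} |
| When is the allocation released? | Not stated | – |
| Is it released singly or as a list? | Not stated | – |
| Is the assigning doctor separate from recruiters? | Not stated | – |
| Who is barred from recruitment and allocation? | rTMS therapists | {17a} |
| Are physicians blinded? | Told the allocation in {16b}; expected to stay blinded in {21a} | {16b}, {21a} |

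**3. Inference on concealment.** The order in {15} protects concealment only if the allocation stays unknown until consent and baseline are complete. No section says so. A doctor assigning according to the sequence suggests access to it. The procedure as stated therefore permits foreknowledge without establishing it.

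**4. Inference on blinding.** {16b} informs doctors without restriction, while {21a} expects physicians' blinding to be maintained. Unless these are different doctors, which the text does not say, the two statements conflict.

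**5. How much could be known in advance (illustration).** Take a fixed 19/19/19 list in random order.
- Guessing by chance: 57 × 1/3 = 19 correct.
- Knowing only past assignments and always guessing the arm with most places left: about 24.3 of 57, or 43% (simulation, 40,000 runs).
- Holding the whole sequence: 57 of 57.

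The fixed list alone adds about 24.3 − 19 = 5.3 correct guesses. Access to the sequence is what matters.

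**6. What a bias would do (assumed sizes).** Two-sample t-test, n = 19 per arm, df = 36, two-sided α = 0.05, critical value 2.028. The noncentrality is δ√(n/2) = δ√9.5.
- δ = 0.2 SD: noncentrality 0.616, rejection probability 0.092.
- δ = 0.3 SD: noncentrality 0.925, rejection probability 0.147.

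Both values of δ are assumptions. Nothing in the document says that this procedure would produce a shift of either size.

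**The case against.** The strongest defence is that the text is compatible with a sound procedure. An independent statistician makes the list, allocations go out by telephone, and assignment follows consent and baseline. If each call concerned one patient and came after baseline, concealment would be good. An article may also leave release timing to the full protocol. This defeats any claim that concealment has failed. It does not settle the point, because what the article does state about concealment is disclosure to doctors, and it gives the act of assignment to a doctor rather than to the statistician.

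A reader might also infer three stronger things that the document does not support:

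- **A doctor holds the full list and knows the next arm.** No section says this. {16c} says only that assignment follows the results of the sequence.
- **The recommending, treating and assigning doctor is one person.** This is plausible from {15}, {16c} and {26a}, but it is not stated. Referral is open to several kinds of staff, and eligibility lies with neurologists.
- **The blinding section {17a} contradicts disclosure to doctors.** It withholds the allocation from patients and from other researchers, which can be read as those not already informed under {16b}. The trial is single-blind, and a therapist delivering active or sham stimulation must know the arm. The conflict lies with {21a}.

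The room for differential care is also narrower than it may appear, given the fixed rehabilitation schedule, the ban on cognition-improving drugs, and the intention to keep patients and evaluators blind.

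**Conclusion.** The point holds in this form: allocation concealment is not secured by the procedure as written, and {16b} and {21a} disagree on whether physicians are blinded. The first part rests on two gaps: no stated withholding of the allocation until consent and baseline are done, and no separation of the assigning doctor from those who recruit. The second rests on reading doctors and physicians as the same group, which nothing in the text excludes.

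Whether any doctor actually has foreknowledge depends on release timing that the article does not give. The size of any bias cannot be estimated from the document, and the 9% and 15% error rates show only what assumed shifts would do. It is still worth correcting, because analysis cannot fully remove selection at entry and the remedy is nearly free.

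**What to change.** 1. **Concealment mechanism {16b}.** Remove doctors from those told the allocation. State that the independent statistician alone holds the list and releases one allocation at a time by telephone, only after eligibility, consent and baseline are recorded, and only to the rTMS therapist.
2. **Implementation {16c}.** Remove the doctor's assigning role and refer to the release procedure above.
3. **Blinding {17a} and data monitoring committee {21a}.** Say explicitly whether recommending and treating doctors are blinded, so that these sections agree with {16b}.
4. **Unblinding {17b}.** Reconcile the statement that unblinding will not be needed with the new arrangement, and describe how a doctor obtains the allocation in a safety event.
5. **Patients already assigned.** Trial status says recruitment is under way. Apply the change to remaining patients, and document and report the procedure used for those already allocated, including who saw the sequence and when.

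**Cost.** A protocol amendment, using the statistician, telephone link and therapist already in place. The small downside is that the allocation sits with the statistician and therapist if a doctor needs it, hence item 4. Keeping treating doctors blind goes somewhat beyond the declared single-blind design, though it matches what {21a} already expects. The change cannot protect patients allocated before it.

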## Assignment of interventions: blinding

### Who will be blinded {17a}

The exact allocation and treatment plan are not disclosed to patients, as well as other researchers such as evaluators and analysts. And rTMS physical therapists are not involved in other research work, such as patient recruitment, randomization, allocation, outcome evaluation, and data analysis.

### Procedure for unblinding if needed {17b}

There will be no need for unblinding throughout the entire research process.

## Data collection and management

### Plans for assessment and collection of outcomes {18a}

This experiment will use a paper case record form (CRF) to record all experimental processes and result in data. To ensure patient privacy, each participant will have a unique identification code. During the registration phase, two data administrators will input the CRF into the computer and check paper and electronic data. The MRIs will be conducted at the Shanghai Herson Rehabilitation Hospital Department of Radiology.

### Plans to promote participant retention and complete follow-up {18b}

During the recruitment process, patients will be provided with comprehensive information about the study, including its setup and requirements. They will also be reminded about the importance of completing the follow-up. Patients can stop at any time during the study and are not obliged to give a reason to discontinue. To assess the patient’s progress, a quality form will be used, and patients will be reminded to cooperate with the researcher’s scale assessment throughout the survey. We will collect any outcome data from participants who have discontinued or deviated from intervention protocols.

### Data management {19}

In this trial, we will use a paper CRF to record all process and outcome data. Each participant will be assigned a unique identification number to protect their privacy. During enrollment, two data managers will input the CRF into the computer and verify both the paper and electronic data. The final trial dataset will be accessible to all study co-applicants and researchers.

### Confidentiality {27}

During the study, research data will be labeled with a unique study identification code for each participant. The key to this identification code list will only be accessible to the research team. After completing the study, the principal investigator will follow research guidelines to document and safeguard the key. No patients identification details will be reported in publications.

### Plans for collection, laboratory evaluation and storage of biological specimens for genetic or molecular analysis in this trial/future use {33}

According to China’s legislation, the leftover material(tested blood samples) will be appropriately treated as medical waste.

## Statistical methods

### Statistical methods for primary and secondary outcomes {20a}

Statistical analysis will be conducted using SPSS version 25.0 and Microsoft Excel 2016 software.

Measurement data (e.g., MoCA BJ, MMSE, TMT, DST, MBI, BDNF, and VEGF levels in serum, TCD) were statistically described by mean ± standard deviation (*x* ± *s*); count data (such as stroke type, hemiplegic side, and stroke risk factors) were described by frequency (*n*) and percentage (%). The measurement data were first tested for normality, and those not conforming to the normal distribution were expressed by M (P25, P75) and analyzed by Kruskal–Wallis H test; the data conforming to the normal distribution were expressed by *x* ± *s*, one-way analysis of variance was used for comparison between multiple groups, LSD-t-test, and paired *t*-test was used for patients before and after treatment. All test levels were significant at *α* = 0.05 and *P* < 0.05.

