### Objectives {7}

The objectives of this study are:To examine the efficacy of conventional treatment in improving cognitive function in stroke patients;To evaluate the efficacy of single target high-frequency rTMS stimulation in improving cognitive function in stroke patients;Explore whether the therapeutic effect of dual-target rTMS on cognitive function in PSCI patients is better than that of a single target; andAnalyze the mechanism of high-frequency rTMS in improving cognitive impairment after stroke using indicators such as brain Doppler ultrasound and serology.

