### Trial design {8}

This study will include a single-blind, 3-arm, parallel design, randomized superiority controlled trial with a distribution ratio of 1:1:1. Eligible patients will be randomly assigned to the conventional treatment group, single target stimulation group, or dual target stimulation group and will receive intervention treatment for 4 weeks each. This research protocol follows the SPIRIT reporting guidelines [8], as shown in Fig. 1.

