### Outcomes {12}

This study measures the effectiveness of rTMS treatment on cognitive ability. Two primary assessments will be conducted, the Montreal Cognitive Assessment Beijing Version (MoCA-BJ) and the Mini-Mental Status Examination (MMSE). In addition, secondary assessments such as the modified Barthel index (MBI), Trail-Making Test (TMT), digital span test (DST), transcranial Doppler (TCD) examination, and serum BDNF and VEGF levels will also be conducted. All assessments will be done twice, pre-treatment (baseline) and post-treatment. A trained neuropsychologist will conduct all cognitive assessments without informing the participants’ cognition status.MoCA-BJ. The MoCA-BJ scale is one of the Chinese versions of the Montreal Cognitive Assessment used to assess general cognitive function [13], which has high sensitivity and specificity for screening cognitive impairment from patients with stroke [14]. The cognitive function was evaluated through alternating connections, drawing cubes, drawing clocks, naming, retelling, subtracting seven from 100, and directional ability. This scale was developed based on MMSE, with a score of 30 points and ≥ 26 points representing normal cognition [15]. A patient’s cognitive function is better if their score is higher.MMSE. The MMSE is a quick and easy cognitive function screening tool commonly used in clinical settings. It takes about 10 min to complete and consists of a single-page, 30-point test that assesses various cognitive domains including memory, attention, and language. A higher score indicates better overall cognitive function, with a score of 27–30 indicating normal function, 21–26 indicating mild impairment, 10–20 indicating moderate impairment, and 0–9 indicating severe impairment [16].TMT(Chinese version). In the TMT-A section, connect the numbers from 1 to 25. TMT-B includes numbers in square and circular shapes, requiring participants to arrange the two forms alternately when connecting numbers in sequence. The scoring criteria are the time taken to complete TMT-A and TMT-B, as well as the interference amount (TMT-B time consumption minus TMT-A time consumption) [17]. This tool is commonly used for diagnosing visual attention, executive function, and processing speed in neuropsychological diseases [18, 19].ADL. The primary activities of daily living are assessed with the modified Barthel Index (MBI) [20], which is used to evaluate individual self-care performance and derived from the Barthel Index. In this study, we used the Chinese version of MBI [21]; it also consists of ten items: personal hygiene, bathing, feeding, toileting, stair climbing, dressing, bowel control, bladder control, ambulation or wheelchair and chair-bed transfer with total 100 scores indicating completed independence. A higher score on the MBI indicates superior independent living ability [22].DST. The scale can be divided into digit span forward (DSF) and digit span backward (DSB), each of which consists of two sets of 2-digit to 10-digit tables. The test begins with item 1 and is stopped after two incorrect attempts. The total score of the DSF and DSB indicates the participant’s attentional functioning, with a higher score indicating better function. A score of less than 5 suggests impaired attention function [23].TCD. According to the latest epidemiological survey, cerebrovascular disease and its risk factors are significant contributors to cognitive decline. By managing these risk factors, it is possible to delay cognitive decline [24]. TCD can assess large vascular lesions and cerebrovascular function, which can provide a basis for early diagnosis and treatment of PSCI [25]. The main indicators for assessment are the average blood flow velocity (Vm), pulsatile index (PI), and resistance index (RI) of the patient’s middle cerebral artery, which measure cerebral hemodynamic changes.Blood sampling. Serum samples will be obtained to analyze BDNF and VEGF levels at baseline and post-treatment. Peripheral venous blood (5 ml) will be collected from 7:00 am to 9:00 am in a climate-controlled room following overnight fasting [26]. The blood was then centrifuged to separate the serum and stored at -80℃ in a refrigerator. Serum levels of BDNF and VEGF will be measured using enzyme-linked immunosorbent assay (ELISA) kits. The steps were followed according to instructions [27]. All samples will be measured by the same technician who is blinded to the patient treatment status. All samples will be evaluated in duplicate and averaged.

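### An unspecified normality test chooses the primary analysis, and only the normal branch names a pairwise comparison, so a primary sent to Kruskal–Wallis has no named dual-versus-single test

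*Protocol article*

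**What the plan says.** All statements are in the Protocol article.

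- Statistical methods {20a} sets a two-stage rule for measurement data, a class that expressly includes MoCA-BJ and MMSE: "The measurement data were first tested for normality".
- Data that fail are summarised by median and quartiles and "analyzed by Kruskal–Wallis H test". That branch ends there.
- For data that pass, "one-way analysis of variance was used for comparison between multiple groups, LSD-t-test", with a paired t-test for before-versus-after comparisons.
- The significance level is common to all tests: "All test levels were significant at *α* = 0.05".
- Objectives {7} includes a pairwise question: "Explore whether the therapeutic effect of dual-target rTMS on cognitive function in PSCI patients is better than that of a single target".
- Sample size {14} rests on the expected MMSE difference between the two intervention groups, which I read as single-target and dual-target.
- Outcomes {12} names MoCA-BJ and MMSE as the two primary assessments. Both are 30-point scales.

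The section does not name the normality test or its level. It does not say whether the test is applied per arm, to pooled data or to residuals, or to post-treatment scores, change scores or both visits.

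**The concern.** Two things are wrong with the rule as written.

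First, the outcome data choose the primary analysis. Because the gate itself is undefined, whoever runs the analysis must settle its details, possibly with the data in view, and those details decide which test is reported.

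Second, the branches are not equivalent. The normal branch names an overall test and a pairwise step; the other names only an overall test. A significant Kruskal–Wallis result says that the three arms are not all alike. It could come entirely from the sham arm differing from the two active arms, with no difference between dual and single. For any primary sent down that branch, the plan names no test of the comparison the trial was sized on.

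**Working it through.** **1. The plan's own figure.** Total 57 with a "distribution ratio of 1:1:1" gives 57/3 = 19 per arm, matching the number blocks 1–19, 20–38 and 39–57 in Implementation {16c}. Both 45/(1 − 0.20) = 56.25 and 47 × 1.20 = 56.4 round up to 57, so the 20% allowance is consistent with the total. The base number cannot be reproduced, because no effect size, SD or power is given. With 20% loss, 19 × 0.8 = 15.2, so about 15 or 16 completers per arm. The plan gives no rate at which normality would be rejected.

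**2. What each branch offers.**

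| | Passes normality | Fails normality |
|---|---|---|
| Overall three-arm test | one-way ANOVA | Kruskal–Wallis |
| Dual versus single | LSD t-test | none named |
| Arm summaries | mean ± SD | median and quartiles |
| Between-arm estimate with interval | none named | none named |

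The difference that bears on the objective is the second row.

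**3. How often the second branch is entered if data are exactly normal.** Assumption: each normality test is run at 0.05, and one rejection moves the outcome to Kruskal–Wallis. For k independent tests, P(at least one rejection) = 1 − 0.95^k.

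- k = 1 (one residual or pooled test): 0.050.
- k = 3 (three arms, post-treatment): 1 − 0.95³ = 0.143. Simulated Shapiro–Wilk with 15 to 19 per arm gave 14–15%.
- k = 6 (three arms, two visits): 1 − 0.95⁶ = 0.265. Simulation with a pre/post correlation of 0.8 gave 24% (16 per arm) and 25% (19 per arm); a separate check on near-normal scores gave 26–29%.

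**4. Other score distributions.** The documents give no outcome SD or shape, so these are assumptions. Shapiro–Wilk at 0.05, 15 to 19 per arm, one outcome, post-treatment:

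| Assumed scores | Per-arm gate | Residual gate |
|---|---|---|
| Rounded, or entry range truncated | 16–18% | 6–9% |
| Baseline uniform on 10–26 | 31–39% | 27–38% |
| Skewed or ceiling-limited | 58–95% | 39–82% |

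For integer change scores (16 to 19 per arm, per-arm gate) the rate is 21–22% with SD 3, 36–37% with SD 2, 56–62% with SD 1.5 and about 95% with SD 1.

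Over these readings the rate runs from about 5% to about 95%. That spread comes from choices and facts the article does not state.

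**5. After the change.** If one analysis and its contrast are fixed whatever the distribution, the chance that a primary has no planned dual-versus-single test is 0 by construction.

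**The case against.** The best defence has three parts.

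*A journal article condenses.* A post-hoc procedure after Kruskal–Wallis is the kind of detail a full protocol or SAP may hold. That would be decisive if the article were simply silent. But it states the gate as a rule, and it names a follow-up test for one branch and not the other. The data-driven choice and the asymmetry are in the text.

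*The two-stage rule may do little harm to error rates.* A simulation of 4,000 null trials (19 per arm, per-arm post-treatment gate, assumed mean 18–19, SD 4, change SD 3) gave an overall type I error of 5.1% for normal data and 5.0% for truncated, capped integer scores, against 4.7% for ANOVA alone. The two tests disagreed on significance in about 2% of trials. This stands under those assumptions: the case does not rest on an inflated overall error rate. But these are omnibus results and do not supply the missing pairwise comparison.

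*The entry limits need not make rejection more likely.* In that simulation the gate fired in 13.9% of trials with truncated scores and 14.6% with normal ones; the assumptions in the second table gave slightly higher rates. No firm claim either way is warranted.

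A reader might also infer several stronger points that the document does not support:

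- *That the plan lacks an effect estimate only in the rank branch.* No between-arm difference or interval is named in either branch, and the rank branch still reports medians and quartiles.
- *That raw scores are tested instead of residuals.* The text does not say. Within one arm at one visit, the two differ by a constant and Shapiro–Wilk gives the same answer.
- *That MMSE and MoCA-BJ results become non-comparable if they take different branches.* They are separate scales, each tested on its own, and different valid tests do not invalidate either.

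**Conclusion.** The point holds in a limited form. The choice of primary analysis depends on the data through an undefined gate, and for any outcome sent to Kruskal–Wallis the plan names no test of dual versus single.

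Its frequency is conditional. For near-normal scores, 19 per arm and Shapiro–Wilk at 0.05, it is about 5% with one residual test, 15% with three post-treatment arms and 26–29% with three arms at two visits. It is higher for skewed or ceiling-limited scores.

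It would be tempting to say that a quarter to a third of such trials would leave the dual-versus-single question untested. The documents do not support that. The figure needs a particular gate (per arm, both visits or both primaries, any single rejection decisive), and nothing says that a baseline rejection would change the post-treatment comparison. A failure on one primary also need not stop the other from reaching ANOVA and LSD.

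**What to change.** For MMSE and MoCA-BJ, remove the normality gate and prespecify one analysis: ANCOVA of the post-treatment score on its baseline value, with the dual-minus-single contrast and its confidence interval reported whatever the distribution looks like. Add one rank-based or permutation sensitivity analysis. The baseline scores are already collected, and the contrast gives an estimate and standard error that can be pooled over the multiple imputations planned in {20c}.

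If the Kruskal–Wallis branch is kept for other outcomes, name a pairwise dual-versus-single follow-up for it.

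The cost is analysis wording and one extra sensitivity analysis. Visits, measurements and sample size do not change.
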